## Abstract

**Background:**

This study seeks to determine if implementing a culturally-appropriate early childhood caries (ECC) intervention reduces dental disease burden and oral health inequalities among Indigenous children living in South Australia, Australia.

**Methods/Design:**

This paper describes the study protocol for a randomised controlled trial conducted among Indigenous children living in South Australia with an anticipated sample of 400. The ECC intervention consists of four components: (1) provision of dental care; (2) fluoride varnish application to the teeth of children; (3) motivational interviewing and (4) anticipatory guidance. Participants are randomly assigned to two intervention groups, immediate (n = 200) or delayed (n = 200). Provision of dental care (1) occurs during pregnancy in the immediate intervention group or when children are 24-months in the delayed intervention group. Interventions (2), (3) and (4) occur when children are 6-, 12- and 18-months in the immediate intervention group or 24-, 30- and 36-months in the delayed intervention group. Hence, all participants receive the ECC intervention, though it is delayed 24 months for participants who are randomised to the control-delayed arm. In both groups, self-reported data will be collected at baseline (pregnancy) and when children are 24- and 36-months; and child clinical oral health status will be determined during standardised examinations conducted at 24- and 36-months by two calibrated dental professionals.

**Discussion:**

Expected outcomes will address whether exposure to a culturally-appropriate ECC intervention is effective in reducing dental disease burden and oral health inequalities among Indigenous children living in South Australia.

## Background

### Early childhood caries (ECC)

Early childhood caries is the presence of one or more decayed, missing, or filled primary teeth in children aged 71 months (5 years) or younger [1]. In children younger than 3 years, any sign of dental decay is considered Severe ECC, or S-ECC [2]. Early childhood caries not only causes pain, but also impacts children’s ability to eat, play and sleep [3]. It is associated with chronic childhood conditions and nutritional disorders [4], and is the strongest predictor of poor oral health later in childhood and into adulthood [5], when it is associated with clinical symptoms as well as psycho-social outcomes such as low self-confidence and poor perceived social acceptability.

### Indigenous Australian ECC disparities

Indigenous Australians are disadvantaged on almost every health and social indicator compared to non-Indigenous Australians [6]. Marked oral health disparities exist between Indigenous and non-Indigenous children in Australia; in some areas Indigenous children have up to five times the prevalence of early childhood caries as non-Indigenous children [7]. In light of how many chronic health conditions Indigenous Australians experience [8], oral health may not seem a priority. Yet oral health has important implications for general health and, crucially, there are interventions of known efficacy for preventing this avoidable disease [9]. If the burden of early childhood caries and associated oral health inequalities experienced by Indigenous children are to be reduced, more needs to be done to ensure that appropriate preventive measures, together with support for maintaining optimal oral health, are provided to carers of Indigenous children in the early life stages.

### ECC intervention rationale

The intervention undertaken in this study is comprised of four approaches reported to successfully prevent early childhood caries: dental care provided during pregnancy [10,11]; fluoride varnish applied to the teeth of children [12-15]; motivational interviewing [16-18]; and anticipatory guidance [19-22]. Most dental care during pregnancy is safe, and may aid in preventing early childhood caries because maternal transmission is the primary way in which children are inoculated with the bacteria, mutans streptococci, associated with early childhood caries. Fluoride varnish prolongs contact between fluoride and enamel and is particularly efficacious in preventing early childhood caries in Indigenous populations [12-15]. Reports indicate little difficulty with compliance and no adverse events; and non-dental personnel can be trained to apply fluoride varnish. Motivational interviewing (MI) is a non-judgmental, client-centred method of engaging intrinsic motivation to change behaviour by developing discrepancy and exploring ambivalence, in this case, about oral health. Employing strategies to move carers from inaction to action, motivational interviewing offers many possible paths to solutions [23]. Anticipatory guidance is a developmentally-based counselling technique that focuses on the needs of a child at particular stages of life. It has been effectively used in the dental setting to reduce ECC among high risk populations [22].

### Aim and hypotheses

This study seeks to determine if implementing a culturally-appropriate early childhood caries (ECC) intervention reduces dental disease burden and oral health inequalities among Indigenous children living in South Australia, Australia. We hypothesize that exposure to a culturally-appropriate ECC intervention will reduce dental disease burden among Indigenous children and reduce oral health inequalities between such children with their non-Indigenous counterparts. The South Australian study described in this paper is part of a larger investigation including research teams in New Zealand and Canada; we will compare findings when they become available.

## Methods

### Intervention review

In this randomised, controlled trial participants are offered four intervention components: (1) provision of dental care; (2) fluoride varnish application to the teeth of children; (3) motivational interviewing and (4) anticipatory guidance. A schema outlining the study design is presented in Figure 1.

1. Provision of dental careIn the test-immediate intervention group, dental care is arranged during pregnancy or up to six weeks after birth. For participants in the control-delayed intervention group, dental care is arranged when their child is 24 months of age. Care will comprise of extractions, restorations, scaling and prophylaxis and will take as many visits as required to achieve a non-diseased mouth. Participants holding an Australian healthcare or pensioner concession card will be eligible for treatment through the South Australian Dental Service; participants who do not hold this entitlement will receive treatment from private dentists limited to $1265 AUD. Dentists are asked to focus on reducing bacterial load, such as filling or extracting teeth with frank carious lesions. Study staff remind participants of dental appointments by telephoning, sending text messages via mobile phone and sending letters, and attempt to mitigate obstacles such as dental fear and lack of childcare by attending appointments when helpful. Free transport to and from the dentist is also available through culturally-sensitive transport providers.

2. Fluoride varnish applicationsFluoride varnish is applied to children by trained study staff in a setting convenient to participants, often their homes. In the test-immediate intervention group, this occurs when children are aged 6-, 12- and 18-months. Children in the control-delayed intervention group receive fluoride varnish applications at 24-, 30- and 36 months. Given the obstacles in meeting participants, these age targets are extended by one month prior and three months following target age, e.g. the six-month meeting can occur anywhere from five to eight months of age.

3. Motivational interviewingParticipants in the test-immediate intervention group receive four motivational interviewing (MI) sessions by trained study staff, with each session focussing on a specific directive. For participants in the test-immediate intervention group, the MI sessions occur at baseline (pregnancy) and when the child is aged 6-, 12- and 18-months. The directives for each of these sessions are: (1) Baseline/pregnancy; encourage participants to attend dental appointments; (2) Child aged 6-months; encourage participants to learn more about the importance of non-cariogenic foods and drinks for their child; (3) Child aged 12-months; emphasise to participants the importance of fluoride in early childhood caries prevention; and 4) Child aged 18-months; encourage participants to enrol their child for a dental check. Participants in the control-delayed intervention group receive three motivational interviews when the child is aged 24-, 30-, and 36 months, with the first session combining directives one and two.

4. Anticipatory guidanceAnticipatory guidance (AG) for those in the test-immediate intervention group will occur during pregnancy and when the child is aged 6-, 12-, and 18-months. Participants in the control-delayed-intervention group will receive anticipatory guidance when the child is aged at 24-, 30-, and 36 months. The anticipatory guidance topics reflect and compliment the directives of the MI sessions.

**Figure 1 F1:**
[figure not shown]
Study design schema.

#### Participants and recruitment

Participants must be pregnant residents of South Australia expecting an Indigenous Australian baby or babies, or who have recently birthed an Indigenous Australian baby or babies less than six weeks of age. Although interventions are timed differently (the test-immediate intervention begins in pregnancy, while the control-delayed intervention begins when the child is aged 24- months), all participants are eligible to receive free dental care including transportation, fluoride varnish for children’s teeth, dental-related sample bags as well as gift cards valued at fifty dollars as reimbursement for time spent completing each questionnaire at baseline, 24- and 36- months. Participants are recruited through referrals from a variety of sources including Indigenous groups, community services and hospitals. Recruitment commenced January 31, 2011 and will end May 4, 2012.

#### Ethics and consent

This study received approval from the University of Adelaide Human Research Ethics Committee, the Aboriginal Health Council of South Australia, the Government of South Australia, the Human Research Ethics Committee of Child, Youth, and Women’s Health Service, and the Human Research Ethics Committees of participating Adelaide hospitals (i.e. Flinders Medical Centre, Lyell McEwin Hospital and Women’s and Children’s Hospital). Researchers receive guidance from an Indigenous reference group and heed the World Health Organisation principles that health research among Indigenous populations needs to be designed and carried out in a manner that takes account of cultural differences based on mutual respect, and is beneficial to both parties [24]. The study also takes into account local Indigenous South Australians’ principles that the project be sustainable, pro-active, and have an Indigenous community and family approach. Researchers are respectful of participants’ time and needs, and link families to other services whenever possible.

Potential participants are provided information about the study face-to-face and/or over the phone from health service providers and study staff. If potential participants consent to meeting, researchers explain the project in detail, answering any questions which arise. Those who want to participate are then asked to complete and sign a form expressing consent for various elements of the study including participation, access to child’s dental records, access to child’s hospital records and audio recording for the purposes of assessing researchers’ proficiency in motivational interviewing. Consent is obtained using the NHMRC Guidelines for Ethical Conduct in Aboriginal and Torres Strait Islander Health Research [25]. All participants are informed that their participation is voluntary and they can refuse or withdraw from participating at any stage without reason or justification. Participants receive a form explaining how to discuss their rights as a participant, raise concerns about the study, and/or make a complaint. Study results will be sent to interested participants.

#### Staff

Four staff have been employed for the Australian arm of the study; one Indigenous and three non-Indigenous.

### Data collection

Clinical and self-reported data collected during interventions are entered into password-protected Microsoft Excel and Access databases at the Australian Research Centre for Population Oral Health, University of Adelaide.

#### Sample size

Based on a recent ECC intervention study of Australian Northern Territory-dwelling Indigenous children, it was estimated that a sample size of 250 (125 in each arm of the trial) would be necessary to detect a 25 percent difference in ECC prevalence between the two groups, at the significance criterion of 0.05 and a power of 0.80 [15]. The literature indicates that it is reasonable to expect a difference in effect of this magnitude following a motivational interviewing intervention among Indigenous children [16]. Allowing for an attrition rate of 35 percent after 36 months, 385 participants would be necessary at base-line; rounded up to 400 for convenience (200 test-immediate intervention group, 200 control-delayed intervention group).

#### Randomisation

Participants are randomly assigned on a 1:1 basis to either a test-immediate or control-delayed intervention group. A computer-generated permuted block randomisation sequence is used, stratified by six recruitment sites, i.e. Women’s and Children’s hospital, Flinders Medical Centre and Southern metropolitan, Lyell McEwin and Northern metropolitan, Whyalla and Port Pirie, Port Augusta, and non-metro regions including Murray Bridge, Mount Gambier, Port Lincoln and Ceduna. The randomisation was developed by biostatisticians at the Australian Research Centre for Population Oral Health (ARCPOH) using a random number generator. Randomly selected block sizes of 4, 6 and 8 were used, such that there is an equal number of participants in each intervention arm within the blocks. This ensures that if the study is stopped at any particular time there will be approximately an equal number of participants in each intervention arm.

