#### Questionnaires

Self-report information in the form of a questionnaire will be administered by staff at baseline (pregnancy) and when children are aged 24- and 36-months. The questionnaire was pilot-tested using focus groups comprised of members of participating Indigenous communities and Aboriginal Maternal Infant Care workers, with the questions revisited and refined during Year 1 of the research. Questionnaire items were modelled on those used in both Australian [26] and international population-level surveys [27,28] and include carers’ self-reported ECC experience of their child, as well as carers’ oral health knowledge, oral self-care, dental service utilisation, oral health-related self-efficacy and oral health literacy.

Covariates include socio-demography, oral health and general health. Socio-demographic covariates (collected at baseline only) include age, Indigenous affiliation, residential location, education level, employment, gross household income, house ownership, number of children, number of people who stayed in house the previous night, and car ownership. Oral health covariates include carer self-reported oral health, oral health-related quality of life, and history and experience of dental services of both the parent and child. General health covariates include parent behaviours such as tobacco smoking, alcohol consumption and self-reported general health.

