### Statistical Analysis

Test-immediate and control-delayed intervention groups will be compared at baseline, 24- and 36- months. Results will be compared using the Generalized Linear Mixed Model (GLMM) approach to focus on variation in the primary outcome: early childhood caries levels. All participants who completed the 24-month follow-up ECC-related outcome data will be included in multivariate modelling. Analysis will include fitting GLMM models for analysis of the correlated data in order to determine factors associated with ECC-related changes. Missing data will be addressed by the GLMM estimating mechanism, which assumes interdependence between repeated measures of participants, copes well with random missing data, allows for different intercepts and rates of change, and provides good predictive models. All variables showing associations at p < 0.15 in the GLMM univariate analyses will be entered into multivariate models using a stepwise approach. All effects will be estimated with 95% confidence intervals, with statistical significance taken as a two-sided p-value less than 0.05. This data will contribute to the inter-country analysis.

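### Randomisation is stratified by six recruitment sites, but the stated covariate rule does not guarantee that site is in the between-arm model

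*Protocol article*

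**What the plan says.** All references are to the protocol article.

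- **Randomisation:** "Participants are randomly assigned on a 1:1 basis to either a test-immediate or control-delayed intervention group". The method is given as "A computer-generated permuted block randomisation sequence is used, stratified by six recruitment sites", and "Randomly selected block sizes of 4, 6 and 8 were used". The six strata run from metropolitan hospitals to a grouped set of non-metropolitan regions.
- **Statistical Analysis:** "Results will be compared using the Generalized Linear Mixed Model (GLMM) approach to focus on variation in the primary outcome: early childhood caries levels". Covariates are then handled by this rule: "All variables showing associations at p < 0.15 in the GLMM univariate analyses will be entered into multivariate models using a stepwise approach". No term is named as always present. The only correlation attributed to the GLMM is within participant: it is a mechanism "which assumes interdependence between repeated measures of participants". Site appears neither as a fixed nor as a random effect.
- **Questionnaires:** "Socio-demographic covariates (collected at baseline only) include age, Indigenous affiliation, residential location", followed by other items. Residential location is the nearest item to site, but it is not the six-level factor used for allocation.

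**The concern.** Blocking within site forces the arms to be balanced across sites. If caries levels differ between sites, that balance removes a source of chance difference between the arms. An analysis without site does not credit the removal. Its standard error is then larger than the true sampling variability of the unadjusted estimate under this design, so the test rejects too seldom under the null and loses power under the alternative.

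Under the stated rule, site either is a candidate, and its place depends on the outcome data, or is not a candidate, and never enters. Neither reading ties the analysis to the strata used for allocation. With a logit link there is a second consequence: the odds ratio is non-collapsible, so the treatment effect being estimated changes with whether site is in the model. At stake are some power and a pre-specified estimand, in a trial planned at 80% power with 35% attrition.

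**Working it through.** **The plan's own figure.** 250 / (1 − 0.35) = 384.6, rounded up to 385, as stated in Sample size. The rounded 400 leaves 400 × 0.65 = 260 evaluable, against 250 required.

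**Inputs from the article.** Six strata; blocks of 4, 6 and 8; 1:1 allocation; 400 randomised; 35% loss; two-sided 0.05.

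**Inputs assumed, because the article gives none.**
- ECC prevalence of 67% against 0.75 × 67% = 50.25%. This reads the stated 25 percent difference as relative. The stated 125 per arm is reproduced on that reading at a control prevalence of about 69%, so 67% is a plausible neighbour.
- Stratum sizes of 90/80/80/50/50/50.
- Loss at random, and one binary ECC outcome at one time point.
- Between-site SD on the logit scale, varied from 0 to 1.2.

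**Check 1: site never in the model against site always in.** Logistic model, 4,000 simulated trials per setting. Monte Carlo standard error is about 0.7 points for power and 0.3 points for type I error.

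| Between-site SD | Power, omitted | Power, included | Difference (points) | Type I error, omitted | Type I error, included |
|---|---|---|---|---|---|
| 0 | 77.4% | 77.7% | 0.3 | 4.7% | 4.8% |
| 0.3 | 75.7% | 76.7% | 1.0 | 4.3% | 4.7% |
| 0.5 | 73.1% | 75.6% | 2.5 | 4.0% | 4.5% |
| 0.8 | 67.8% | 73.0% | 5.2 | 4.3% | 5.2% |
| 1.2 | 57.2% | 68.5% | 11.3 | 3.4% | 5.0% |

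Including site costs nothing detectable when sites do not differ. Type I error with site omitted stays below 5% throughout.

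**Check 2: would the p < 0.15 screen retain site, if it is a candidate?** Treat the univariate test as chi-square on 5 df with non-centrality 260 × 0.67 × 0.33 × SD² = 57.5 × SD², and compare it with the 0.85 quantile of the central distribution.
- SD 0.3: non-centrality 5.2, passes with probability 59%.
- SD 0.5: non-centrality 14.4, passes with probability 94%.
- SD 0.8: non-centrality 36.8, passes with probability essentially 100%.

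**Check 3: the screened rule itself.** 3,000 replicates per setting, same strata, blocks and loss; control prevalence 67%, log odds ratio 0.71, no other covariates.

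| SD | Never in | Forced in | Screened at 0.15 | Forced − never | Forced − screened |
|---|---|---|---|---|---|
| 0.3 | 78.0% | 78.9% | 78.6% | 0.9 | 0.3 |
| 0.5 | 77.0% | 79.4% | 79.1% | 2.4 | 0.3 |
| 0.6 | 74.5% | 77.9% | 77.8% | 3.4 | 0.1 |
| 0.8 | 71.9% | 76.0% | 76.0% | 4.1 | 0.0 |
| 0.9 | 70.3% | 75.9% | 75.8% | 5.6 | 0.1 |

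Adding a retention step at p < 0.05 changed screened power by at most 0.2 points. Type I error under the screen at SD 0.9 was 5.0%.

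**Check 4: the interval.** Adding site raised the median standard error of the log odds ratio from 0.257 to 0.268 at SD 0.5, and from 0.257 to 0.281 at SD 0.9. Power still rises, because the site-conditional log odds ratio lies further from zero.

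**The case against.** The strongest reply is that the article does not leave site out. It says nothing either way: the rule's reference to all variables may cover site, residential location may carry part of the same information, and the full analysis plan, where model terms are usually listed, is not shown. The screen may also belong only to the models that look for factors associated with ECC change, since it follows that sentence and not the one on comparing arms. If site is a candidate, Check 3 shows that the stated rule performs almost as well as forcing site in. The between-site SD, on which the whole size rests, is nowhere in the article.

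Most of this stands and limits the point. It does not remove it. The article goes beyond silence: it states a selection rule with no exemption, does not confine that rule to the factor-finding models, and lists covariates without recruitment site. Checks 2 and 3 also assume that site is a candidate, which that list does not support.

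Four stronger readings are tempting and should not be drawn:
- That the analysis excludes site. The text neither names it nor rules it out.
- That false positives are inflated. The error runs in the conservative direction.
- That adjustment would narrow the interval. In a logistic model, Check 4 shows the standard error of the log odds ratio rising.
- That the sample size is wrong. The inflation to 385 is correct, and nothing here contradicts a stated figure.

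**Conclusion.** The point holds in a limited form: the plan does not guarantee that the factor used to stratify the randomisation is in the between-arm model.

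- **If site predicts ECC and is left out,** the power loss is about 0 to 3 points for a between-site logit SD up to 0.5 and about 4 to 5 points at 0.8, with a conservative test.
- **If site does not predict ECC,** nothing is lost.
- **If site is a candidate in the screen,** the power loss is at most about 0.3 points. What remains is that the model, and with it the odds ratio being estimated, is settled by the outcome data.

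These sizes rest on assumed prevalences, stratum sizes and between-site variation, on loss at random, and on a single binary outcome in place of the repeated-measures GLMM. The direction follows from the design; the size is illustrative. This is an inexpensive improvement in pre-specification and does not threaten the trial's validity.

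**What to change.** Add one sentence to the Statistical Analysis section: the recruitment-site factor used in the randomisation, with its six levels, enters every between-arm ECC model as a fixed effect whatever its p-value, and is exempt from the p < 0.15 screen and the stepwise procedure. Residential location should not stand in for it.

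The cost is that sentence and five degrees of freedom. Site must be known for every participant in order to randomise, so no new data are needed, and including it cost no detectable power even with no site differences. The result should be described as a site-conditional odds ratio.
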